### Statistical analysis

Primary analyses of the outcomes will be undertaken on an intent-to-treat basis, including all participants randomised regardless of treatment actually received or withdrawal from the study. Mixed models repeated measures (MMRM) analyses will be used because of the ability of this approach to include participants with missing data. This approach will also allow potential clustering effects (students within the same school being more alike) to be explored and accounted for within the analyses. If required appropriate transformations of scores will be undertaken. Should outliers or distributional problems prelude standard methods, generalized mixed models will be applied. A series of analyses will be conducted to assess the effectiveness of the e-couch Anxiety and Worry program in preventing and reducing symptoms of generalised anxiety. These analyses will include a general analysis of intervention effects comparing the two delivery method conditions to the wait-list control condition, as well as separate analyses to test the effectiveness of the individual delivery methods. MMRM analyses of the secondary variables (for example, depressive symptoms, anxiety stigma) will also be conducted.

Subsample analyses will also be conducted with participants who scored above and below the clinical cutoff scores for anxiety and depressive symptoms at pre-intervention. The preventive subsample analyses will be conducted to identify the true preventive effects of the intervention, while the clinical subsample analyses will be undertaken to provide valuable information regarding the utility of the e-couch Anxiety and Worry program as an indicated intervention. MMRM ANOVAs, identical to those applied to the full sample, will be conducted on the four subsamples of participants. In addition to this, analyses will be conducted to identify any significant differences in the proportion of participants in the intervention and wait-list control conditions who meet criteria for clinical caseness at post-intervention, 6- and 12-month follow-up in the preventative sub-sample analyses, or remain clinical cases in the clinical subsample analyses (attributable risk reduction). The number needed to treat (NNT) will be calculated with 95% confidence intervals (CIs).

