### Sample size and power calculations

Assuming an average class size of 25, a total of 750 students will be available in 30 classes. Based on our previous work [24], we anticipate an intraclass correlation (ICC) of 0.02 and non-participation rate of 30%, with 5% of this non-participation/completion arising from students leaving the school or being absent on measurement occasions. The majority of non-participation (estimated at 25%) will result from failure to return parental consent forms resulting in an inability to participate in the study. In the current study, we plan to address this problem by using electronic communication with parents. We anticipate that this will result in data from 525 students being available. The ICC of 0.02 leads to a design effect of 1.48 and an effective sample size of 354. Assuming a correlation between measurements over time of 0.5, two-tailed tests and alpha of .05, the trial would have 80% power to detect group differences down to 0.3 standard deviations. A group difference of 0.3 standard deviations is marginally higher than the effects obtained using MoodGYM as a universal intervention but, as the current intervention is specifically aimed at anxiety, a slightly larger effect can be reasonably expected. The magnitude of the incremental effect arising from adding *headspace* support to the e-GAD school method condition is uncertain. Comparison of the school method and health service method conditions could be conceptualized within a non-inferiority framework [43] however the sample size required using a defensible non-inferiority margin would be unfeasible. Given the additional costs and resources associated with providing health service support, it was considered acceptable to power the trial to be able to detect differences between the two active conditions comparable in magnitude to comparisons with the wait-list control condition.

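### The repeated-measures models are described without baseline adjustment; constraining or adjusting for the pre-intervention score would cut the standard error of a single-occasion contrast by about 10% to 13%

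*Protocol article*

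**What the plan says.** In the protocol article, Study design lists pre-intervention as one of four occasions, with post-intervention, 6 months and 12 months. Statistical analysis states that "Mixed models repeated measures (MMRM) analyses will be used because of the ability of this approach to include participants with missing data". The subsample paragraph of that section refers to "MMRM ANOVAs, identical to those applied to the full sample", so the ANOVA label covers the main models too. No section says whether the pre-intervention score is a response, a covariate or constrained to be equal across arms, and none names a single primary contrast.

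Sample size and power calculations gives the planning figures. It starts from class size: "Assuming an average class size of 25, a total of 750 students will be available in 30 classes". The design effect is put at 1.48, from an ICC of 0.02, which leaves 354 effective students. The test settings are "Assuming a correlation between measurements over time of 0.5, two-tailed tests and alpha of .05"; and the conclusion is that "the trial would have 80% power to detect group differences down to 0.3 standard deviations". It applies the same target to the comparison of the two active conditions. Table 1 shows the symptom, wellbeing, personal stigma, literacy and help-seeking scales collected at pre-intervention as well as at every later occasion.

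**The concern.** A repeated-measures ANOVA over four occasions, with separate baseline means for each arm, estimates the intervention effect as a difference between arms in change from baseline. Under randomisation the true baseline means are equal. A model that does not use this fact gives away precision. Constraining the baseline means, or conditioning on the baseline score, is never less efficient than the change contrast in large samples, and at a correlation near 0.5 it is clearly better.

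What is at stake is precision, not bias. Only about 10 schools are randomised to each arm, so chance differences in baseline anxiety are to be expected. The change contrast subtracts such a difference in full, when the data support subtracting only part of it. The article's Trial status section says recruitment had closed, so the sample could not grow. Baseline adjustment is a gain still available from scores already collected.

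**Working it through.** **Inputs.** From Sample size and power calculations: two-sided alpha 0.05; effect 0.3 SD; correlation between occasions rho = 0.5; ICC 0.02; 25 students per class; 30 classes; 525 students with data; effective sample size 354. Assumed here, because not stated: equal allocation to three arms; one class per school, hence 10 schools per arm; equal correlation between all pairs of occasions; normal reference distribution.

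**The plan's own figures.** Design effect 1 + (25 − 1) × 0.02 = 1.48, and 525 / 1.48 = 354.7. This agrees with the stated 1.48 and 354. Per arm, 354 / 3 = 118.

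Power = Φ(0.3 / SE − 1.96), with SE = √(2v / n) for n effective students per arm and variance factor v. The stated 80% reproduces as 80.6% in two ways:
- 118 per arm, pairwise, mean of three follow-ups: v = (1 + 2 × 0.5) / 3 = 0.667.
- 354 split into two groups of 177, one occasion: v = 1.

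The article does not say which route was used.

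**Variance factors at one occasion, rho = 0.5.**
- Follow-up score only: v = 1.
- Change from baseline: v = 2(1 − rho) = 1.00.
- Baseline-adjusted: v = 1 − rho² = 0.75.

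SE ratio, adjusted to change: √0.75 = 0.866, so 13% smaller.

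**Power with 118 effective per arm.**

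| Contrast | Change from baseline | Baseline-adjusted |
|---|---|---|
| Pairwise, one occasion | v = 1, 63.5% | v = 0.75, 75.8% |
| Pairwise, mean of three follow-ups | v = 0.667, 80.6% | v = 0.667 − 0.25 = 0.417, 94.6% |
| Both active arms pooled v control (236 v 118), one occasion | 75.8% | 86.7% |

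**Sensitivity to rho (pairwise, one occasion).** At rho 0.3, 49.5% to 67.6%. At rho 0.7, 84.5% to 89.7%. With rho 0.5 and a t reference on 18 degrees of freedom, 58.7% to 71.1%.

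**Sensitivity to the school effect over time.** Applying the full design effect to a change score assumes that the school effect correlates over time no more strongly than the students' scores do. To relax this, take 10 schools per arm and 25 × 0.7 = 17.5 students per school. Let the school variance be 0.02 and the student variance 0.98, with total covariance between occasions 0.5. A school mean has variance A = 0.02 + 0.98 / 17.5 = 0.076. Let B be the covariance of a school's baseline and follow-up means. The change contrast then has SE² = 2 × 2(A − B) / 10, and the adjusted contrast has SE² = 2(A − B² / A) / 10.

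- *School correlation 0.5:* B = 0.01 + 0.49 / 17.5 = 0.038. SE 0.1233 (change) and 0.1068 (adjusted), so 13% smaller. Power 68% to 80%.
- *School correlation 0.8:* B = 0.016 + 0.484 / 17.5 = 0.0437. SE 0.1137 and 0.1009, so 11% smaller. Power 75% to 84%.
- *School correlation 1 (stable effect):* B = 0.02 + 0.48 / 17.5 = 0.0474. SE 0.1069 and 0.0963, so 10% smaller. Power 80% to 88%.

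In this layout the follow-up-only contrast has SE² = 2 × 0.076 / 10 and 68% power throughout. The step from 64% to 68% at school correlation 0.5 comes only from using 17.5 rather than 25 students per cluster in the design effect (1.33 instead of 1.48).

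**The case against.** The strongest reply is that the article never fixes the role of the baseline score. Four occasions describes data collection, the ANOVA label occurs once, and an MMRM with baseline as a covariate is compatible with the text. A condensed article commonly leaves such detail to the analysis plan. This stands in part: the change-from-baseline model is the likely reading, not a stated choice, and silence on covariates is not in itself an error. If the full plan already adjusts for baseline, only confirmation is needed.

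A reader might also infer that the trial has only 64% power and misses its stated 80%. The documents do not support that. The 64% belongs to a pairwise, single-occasion contrast with school effects correlated at only 0.5 over time. The article does not name that contrast as primary and gives no school-level correlation. Averaging three follow-ups, or a stable school effect, brings the change contrast to about 80%. Nor is that contrast always no better than ignoring baseline: this holds at one occasion when both correlations are 0.5, but with a stable school effect it has 80% power against 68% for follow-up only.

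Two further points stand. Chance imbalance does not bias either contrast under randomisation, because it is already in the standard error. And adjustment is not free in every form: a baseline covariate can drop students who lack a pre-intervention score, contrary to the article's stated reason for choosing MMRM.

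**Conclusion.** The point holds as a worthwhile improvement, on an inferred reading of the model. If the models take the pre-intervention score as an unconstrained response, baseline adjustment shortens the standard error of a single-occasion contrast by about 10% to 13% at the plan's rho. Power rose in every scenario examined, by about 5 to 18 percentage points depending on the contrast, rho and the stability of school effects. These figures rest on equal allocation, one class per school, equal correlation between occasions and complete data. They do not show that the stated 80% is wrong.

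**What to change.** State the role of the pre-intervention score. In the primary and secondary MMRMs for outcomes measured at pre-intervention, keep that score in the response vector and constrain its mean to be equal across arms (constrained longitudinal model). With complete data this is about as efficient as covariate adjustment, and it keeps every student with at least one measurement.

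The alternative is to model the three follow-ups with baseline score by time as a covariate. The text should then say how students without a baseline score are handled, since they are otherwise lost.

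The cost is one line of plan text and model code, with no new data. It is best settled before outcomes are analysed.

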## Methods

### Study design

This study will be implemented as a three-arm cluster stratified randomised controlled trial (RCT) with two interventions conditions (e-GAD school method condition and e-GAD health service method condition) and a wait-list control condition. There will be four measurement occasions: pre-intervention, post-intervention, 6- and 12-month follow-up. This study was granted ethical approval by the Australian National University Human Ethics Committee (protocol number 2010/550) and the individual Sate and Territory Education Departments responsible for each participating school.

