### Recruitment

At least 30 schools from across Australia will be recruited to participate in the trial. Schools will be drawn from rural and metropolitan areas and male and female adolescents in grades 9 to 12 (aged 14 to 18 years) will be invited to participate. Schools will be recruited according to the location of participating *headspace* centres. Information letters will be sent to each school informing them of the project. A briefing day will be held for all participating schools prior to the trial’s implementation. The briefing day will provide schools with an opportunity to meet other schools involved in the trial and to receive detailed information and instruction on the delivery of the trial. Information and consent forms will be distributed to all invited participants and their parents/guardians, with written informed consent required from both.

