### Randomisation

Each participating school (cluster) will be randomised to one of the three conditions. Randomisation will occur according to *headspace* centre location. Cluster randomisation will be employed for administrative convenience, to avoid wait-list control condition contamination, and for the ecological validity of providing the intervention at the cluster level [25,26]. A statistician not involved in the implementation of the trial will randomly allocate schools within each *headspace* centre to the intervention or wait-list control conditions using a computerised random number generator. The identity of schools will be concealed from the statistician during this process.

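### Schools are randomised within headspace centres, but the stated analysis accounts only for school clustering and does not name the centre stratum

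*Protocol article*

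**What the plan says.** The Study design section of the protocol article calls the trial a stratified cluster trial with three arms. The Randomisation section makes the school the unit: "Each participating school (cluster) will be randomised to one of the three conditions". It also gives the stratum, since an independent statistician will "randomly allocate schools within each *headspace* centre to the intervention or wait-list control conditions". On numbers, Recruitment says "At least 30 schools from across Australia will be recruited to participate in the trial".

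The Statistical analysis section plans an intention-to-treat mixed model: "Mixed models repeated measures (MMRM) analyses will be used because of the ability of this approach to include participants with missing data". On the design structure it says that this approach will allow "potential clustering effects (students within the same school being more alike) to be explored and accounted for within the analyses". Headspace centre does not appear in that section as a fixed effect, a random effect or a covariate.

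**The concern.** An analysis should normally carry the structure of the randomisation. Here that structure has two levels, schools and the centres within which they were allocated, and the analysis text names one.

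Centre could plausibly matter. Schools were recruited by centre location, so schools in one stratum share a locality. Centre staff help in the classroom in one arm, and the local centre is the referral destination for school counsellors in the teacher-supervised arm (Procedure).

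Stratified allocation balances arms across centres, so centre differences largely cancel from the arm contrast. A model that ignores centre still counts those differences as noise. Standard errors are then too large and power is lost. The loss would matter most for the comparison of the two active arms, which the sample size section also wants to detect at a difference similar to that against control.

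**Working it through.** **Inputs from the Sample size and power calculations section.** ICC 0.02; class size 25 ("Assuming an average class size of 25, a total of 750 students will be available in 30 classes"); 525 students with data; target difference 0.3 SD; two-sided alpha 0.05.

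**Inputs assumed.** The protocol gives neither the number of centres nor the share of the ICC lying between them. I take 10 centres with one school per arm in each (10 schools per arm), one class per school, and centre shares from 0% to 75%.

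**1. The plan's own figures.** Design effect = 1 + (25 − 1) × 0.02 = 1.48. Effective sample size = 525 / 1.48 = 354.7, stated as 354. Both reproduce. They allow for clustering by school or class; centre plays no part.

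**2. Variance of a school mean.** Students per school = 525 / 30 = 17.5. With total variance 1, the variance is 0.02 + 0.98 / 17.5 = 0.02 + 0.056 = 0.076.

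**3. Standard error of a pairwise arm contrast.** With complete blocks the centre component cancels, so with centre variance c (share × 0.02):

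- actual SE = √[2 × (0.076 − c) / 10]
- SE from the school-only model = √(2 × 0.076 / 10) = 0.1233

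| Centre share of ICC | c | Actual SE | School-only SE | Ratio |
|---|---|---|---|---|
| 0% | 0 | 0.1233 | 0.1233 | 1.00 |
| 25% | 0.005 | 0.1192 | 0.1233 | 1.035 |
| 50% | 0.010 | 0.1149 | 0.1233 | 1.073 |
| 75% | 0.015 | 0.1105 | 0.1233 | 1.116 |

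**4. Degrees of freedom.** School-only: 30 − 3 = 27. With centre fixed: 27 − 9 = 18.

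**5. Simulation.** 40,000 trials per scenario, on school means at one time point without baseline adjustment, using t tests with 27 and 18 df:

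| Centre share | Type I error, school-only | Type I error, with centre | Power at 0.3 SD, school-only | Power at 0.3 SD, with centre |
|---|---|---|---|---|
| 0% | 4.9% | 4.9% | 65.3% | 63.7% |
| 50% | 3.9% | 5.2% | 66.3% | 69.7% |
| 75% | 3.1% | 5.1% | 66.6% | 72.8% |

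The simulation standard error near 5% is √(0.05 × 0.95 / 40,000) = 0.11 points, so the model with centre is at or close to nominal throughout. The school-only model is conservative once centre has a share. Adding centre gains 3.4 points of power at a 50% share and 6.2 at 75%, and loses 1.6 at 0%.

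The power levels belong to this simplified analysis and should not be set against the protocol's 80%; only the differences are informative. The planned model also uses the pre-intervention measurement, which would absorb part of any centre difference that is stable over time, so the gain in practice may be smaller.

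**The case against.** The best defence is that a condensed article which names the model class and the clustering level need not list every term. Not mentioning centre does not exclude it, and covariate lists usually sit in an analysis plan, which is not shown. The harm is also conservative and depends on a centre share that nobody has stated. Much of this stands, and it limits the weight of the point. It does not remove it, because the section does say which dependence the model will handle and defines it as similarity within a school. The stratum is missing from the one statement that links the analysis to the design.

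Two stronger readings are tempting, and the document supports neither.

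- *School clustering might be dropped after exploration.* A reader could infer this from the words potential and explored. Ignoring school would give a true alpha of 2 × [1 − Φ(1.96 / √DE)]: 8.9% at a design effect of 1.33 (17.5 per school) and 10.7% at 1.48. But the same sentence says clustering will be accounted for, and the sample size already allows for it. Those figures describe an analysis that is not planned.
- *Tests may be too liberal with so few schools.* Using z in place of t would give about 6.0% with the 27 df of the school-only model, or 6.6% with the 18 df that arise only once centre is added. The protocol states no reference distribution, and that detail commonly belongs to the analysis plan.

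**Conclusion.** The point holds as a modest one about efficiency and calibration. The protocol stratifies by headspace centre, and its stated analysis names only school. With school retained, leaving centre out makes standard errors between 0% and about 12% too large for centre shares of 0% to 75%, and type I error falls to between about 5% and 3%. A larger share would cost more, but would leave almost no variation between schools under the same centre.

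The size rests on the assumed 10 complete blocks of three schools and the assumed shares. The direction depends only on school clustering being kept and centres differing at all. The trial's validity is not in question, and no claim of inflated type I error is made.

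**What to change.** In the Statistical analysis section, or in the analysis plan before the data are analysed:

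- Include headspace centre as a stratum effect in every outcome model, primary, secondary and subsample. Use a fixed effect, or a random effect if there are many centres relative to schools or some centres do not contain all three arms.
- State that the school random effect is retained in every model whatever its estimated size. This only makes firm what the section already says about accounting for clustering.

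The cost is a change of wording. No data, recruitment or allocation is affected, and the Trial status section says data collection was still under way. The statistical price is the between-school degrees of freedom, about 27 falling to 18 if centre is fixed with 10 centres. In the simulation that cost between 1 and 2 points of power when centres did not differ, against a gain of about 3 to 6 points when they held half to three quarters of the ICC.

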## Discussion

In Australia, as in most countries, very few prevention programs for mental health are implemented in schools outside of the trial context, even though there is evidence for their effectiveness. The aim of the current project is to address this problem by trialling two implementation methods that support the delivery of these programs by teachers in the classroom. If demonstrated effective, a new service delivery model for the implementation of mental health prevention programs in schools could be introduced nationally. Such a model would significantly contribute to the mental health of young Australians by providing preventive interventions for mental health problems and consequently reduce the need for clinical services.

Approximately 600,000 young Australians experience a mental health problem. Based on population estimates, and a fully implemented universal program, it is likely that school-based intervention programs could reduce this rate by approximately 14% to 21% [44] thereby conservatively reducing the number with a disorder by as many 90,000. To be feasible, these programs need to be conducted by school teachers. Unlike other school-based programs, the active component of this intervention is delivered automatically online and does not require the training of teachers or the use of specialist psychologists. To our knowledge, this will be one of the first intervention trials for anxiety delivered primarily through the web in school environments. It is also the first trial to compare the effectiveness of different methods of delivering the program, and it has specific and applied implications for prevention delivery across Australia.

